#### *The weight and lifestyle inventory (WALI)*

The WALI is designed to obtain demographics information, weight and dieting histories, eating and exercise habits, and relationships with family and friends [133]. The Portuguese version (IPEV) and the process by which it was translated is published in a national book [134]. The PICO project will use only the sections G, K and Q of the Portuguese version (IPEV) for controlling alcohol and tobacco consumption, dietary patterns and clinical historic.

### Inflammatory biomarkers

Our primary measures are IL-6 and IL-10. These cytokines are consistently implicated in OA pathogenesis and showed significant improvement with weight loss in ADAPT. We will also measure hsCRP as an overall marker of chronic inflammation and TNFα and TNFα soluble receptor 1 (sTNFR1) because they are also implicated in OA pathogenesis. Leptin, an adipokine that increases synthesis of TGFβ, a known stimulator of osteophyte formation, will also be measured.

For assessing IL-6, IL-10, hsCRP, TNFα, sTNFαR1 and leptin, venous blood samples (approximately 10 ml per visit) will be collected into dry tubes and EDTA tubes by standard procedures in the morning after a minimum of 4 h fast without any type of exercise.

Blood will be centrifuged at 1500 x g for 10 min to separate serum from the cloth in the dry tubes and plasma from red blood cells in the EDTA tubes. Serum and plasma will be frozen at 80°C for posterior analysis by ELISA using commercially available kits.

### Statistical analysis

Descriptive statistics, including frequencies for categorical variables and means with standard deviations (SD) for continuous variables with normal distribution and median for skewed distributions will be used to describe subject’s characteristics. Normality will be tested using the Kolmogorov-Smirnov test. For continuous outcome measures, differences in mean change (baseline minus post-intervention) will be compared between groups using analysis of covariance adjusted for baseline values of the outcome. Comparisons between groups (CG and AEG) at baseline and post intervention will be conducted by Independent-sample t-tests or Mann–Whitney U test if equal variance is not assumed. Changes within group will be analyzed by paired Student’s t tests or by the Wilcoxon Signed Rank test when normality is not assumed. A mixed model analyses of covariance (ANCOVAs) will be conducted for interaction analyses adjusted for BMI with two within-participant factors of 6MWT (baseline) and 6MWT (post-intervention) and between two groups (CG and AE). Statistical analysis will be performed using IBM SPSS Statistics 20.0 and MedCalc Statistical Software (MedCalc Software, Mariakerke, Belgium). Multiple Linear regression analyses will be performed to understand the potential covariates that could improve the explanation of the variability of outcomes (6MWT, strength and KOOS dimensions). Statistical significance will be set at P *<* 0.05 (2- tailed) for all analyses. Effect sizes will be calculated for all measures with an effect size of 0.2 considered small, 0.5 medium and 0.8 large.

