#### *Sample*

Considering the calculation of the sample size, the studies of Messier (2009) [74] and Wang (2007) [44] were used as a reference, because they had a sample with similar characteristics and studied similar outcomes. Both showed that a reduction of symptoms in patients with OA of the knee led to a significant improvement (α < 0.05) of the primary outcome measure of self-reported physical function. To find an analogous improvement of self-reported physical function of approximately 25% between the baseline and final measurements in patients with KOA, the minimum number of patients that are required is 20 for the main outcomes. The latter number is based on a power (1-B) of 0.80 and a significance level of 5% (two-sided). When a dropout rate of 20% is taken into account, at least 25 participants must be involved at study onset.

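### The unpaired fallback is tied to the wrong condition: unequal variances lead to Mann-Whitney, which does not hold 5% as a test of equal means when spreads differ

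*Protocol article*

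**What the plan says.** All of the relevant text is in the Statistical analysis section of the protocol article.

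- **Main between-group analysis:** "For continuous outcome measures, differences in mean change (baseline minus post-intervention) will be compared between groups using analysis of covariance adjusted for baseline values".
- **Unadjusted between-group comparisons, at baseline and post-intervention:** "Independent-sample t-tests or Mann–Whitney U test if equal variance is not assumed".
- **Within-group changes**, in the next sentence: "paired Student’s t tests or by the Wilcoxon Signed Rank test when normality is not assumed".
- **Significance level:** "Statistical significance will be set at P *<* 0.05 (2- tailed) for all analyses".

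The two rank tests therefore have different triggers. The unpaired one follows from unequal variance, the paired one from non-normality. The article does not say how equality of variance is to be judged.

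**The concern.** Mann-Whitney takes its null variance from the assumption that both arms share one distribution. If the means are equal but the spreads differ, that variance is wrong, and the test rejects too often or too seldom depending on which arm is larger. The rule thus moves the analyst to a rank test in the very situation where that test loses its 5% level for equal means. Welch's t test is the matching remedy for unequal variance.

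The reverse case is also mishandled. A skewed outcome whose spread is similar in both arms does not trigger the rank test and stays with the ordinary t test.

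The post-intervention P values are at stake. Because the 5% threshold applies to every analysis, they can be reported as evidence alongside the ANCOVA.

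**Working it through.** **1. Inputs and the article's own figure.** The test rule carries no number. The only related figure that can be reproduced is the dropout step under Sample: 20/(1 − 0.20) = 25, as stated. The Abstract gives 50 participants and the Inclusion criteria give 56. No allocation ratio is stated. Assuming 1:1, arms start at 25 or 28. A 20% loss in one arm only gives 25 v 20. A count of 28 v 20 needs a loss of 1 − 20/28 = 28.6% in one arm and none in the other.

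**2. Why Mann-Whitney drifts.** Take normal data with equal means, arm sizes m and n, and SDs σx and σy. U is still centred correctly. Its assumed variance, divided by mn, is (m + n + 1)/12. Its true variance, divided by mn, is

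1/4 + (n − 1)·arcsin(ρx)/2π + (m − 1)·arcsin(ρy)/2π,

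with ρx = σx²/(σx² + σy²) and ρy = 1 − ρx. The rejection rate is about 2·[1 − Φ(1.96/√R)], where R is true variance over assumed variance.

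- 20 v 20, SD ratio 2 (ρ = 0.8, 0.2): true 0.25 + 19(0.1476 + 0.0320) = 3.66; assumed 41/12 = 3.42; R = 1.07; rejection 5.8%.
- 20 v 20, SD ratio 3 (ρ = 0.9, 0.1): true 0.25 + 19(0.1782 + 0.0159) = 3.94; R = 1.15; rejection 6.8%.
- 20 (SD 3) v 25 (SD 1): true 0.25 + 24(0.1782) + 19(0.0159) = 4.83; assumed 46/12 = 3.83; R = 1.26; rejection 8.1%.
- 28 (SD 2) v 20 (SD 1): true 0.25 + 19(0.1476) + 27(0.0320) = 3.92; assumed 49/12 = 4.08; R = 0.96; rejection 4.5%.

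**3. The rule as a whole.** This was simulated as Levene's test at 5% (an assumption), then Student's t if not significant and Mann-Whitney if significant. Data are normal with equal means, two-sided alpha is 0.05, and there are 20,000 runs per cell (simulation error about 0.15 points). Percentages are rejection rates.

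| Arms | SD ratio 1.5 | SD ratio 2 | SD ratio 3 |
|---|---|---|---|
| 20 v 20 | 5.1 | about 5.5 | about 6.5 |
| 25 v 25 | 4.9 | 5.3 | 6.9 |
| 28 v 28 | 5.1 | 5.8 | 6.8 |
| 25 v 20, smaller arm more variable | 5.6 | 6.7 | 8.2 |
| 25 v 20, larger arm more variable | 4.5 | 4.7 | 5.4 |
| 28 v 20, smaller arm more variable | 5.9 | 6.9 | 8.9 |
| 28 v 20, larger arm more variable | 3.9 | 3.8 | 4.9 |

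The 20 v 20 row summarises separate smaller runs. Those also put 25 v 20 with the smaller arm more variable at 6.3–6.4% for ratio 2 and 8.1% for ratio 3. A repeat with 100,000 runs per cell agreed with every cell to within 0.4 points. Welch's t test gave 4.7–5.3% throughout, including with equal SDs.

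**4. The reverse case (assumes lognormal outcomes).** With identical lognormal arms of 20 to 28 and log-SD 0.5 to 1.0, the variance trigger selects Mann-Whitney in only 10–19% of trials. With a shift of 0.8 SD on the log scale and 25 per arm, the rule has 72%, 66% and 61% power at log-SD 0.5, 0.8 and 1.0. Using Mann-Whitney throughout gives about 77%.

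**The case against.** The strongest reply is that the affected tests do not carry the treatment effect. That stands: the between-group contrast on change is the baseline-adjusted ANCOVA, and the clause governs only supporting comparisons.

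The second reply is that the inflation needs a special null. If exercise does nothing to an outcome, both arms share one distribution. The rule then rejects 4.9–5.0% for normal data and 2.7–3.3% for lognormal data. At baseline, randomisation puts the arms in this position, so the baseline comparisons are essentially safe. If only one arm responds on average, the means differ and a type I error figure does not apply. This also stands. The error arises post-intervention when spreads differ but means do not, for example when responses vary without a net shift. That is narrow, but unequal spread is the condition for which the clause was written.

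A reader might infer more than the article supports:

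- *That both fallbacks are wrong.* The paired Wilcoxon test is tied to non-normality, which is a suitable trigger.
- *That the biomarker ANCOVA is invalid.* The article does not describe the cytokine distributions, and a transformation may be left to a fuller plan. If lognormal data are assumed, raw-scale ANCOVA does not inflate false positives (3.7–4.9%). The cost is power only.
- *That the Kolmogorov-Smirnov test makes matters worse.* "Normality will be tested using the Kolmogorov-Smirnov test", but nothing links its result to the ANCOVA or to the choice between t and Mann-Whitney.

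**Conclusion.** The clause is wrong as written, and the consequence is modest. With normal data, equal means and an SD ratio of 2 to 3, the rule rejects about 5.5–6.5% with 20 per arm. At 25 v 20 it rejects about 6.3–8% when the smaller arm is the more variable. It can drop to about 4% when the larger arm is the more variable, seen at 28 v 20 with SD ratios of 1.5 to 2. Welch holds about 5% in all of these. At an SD ratio of 1.5 with equal arms the rule causes no visible harm.

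These figures rest on three assumptions that the article does not state: 1:1 allocation, Levene's test at 5% as the variance check, and the SD ratios.

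Welch is not a cure for everything. With lognormal data, equal means, 25 per arm and log-SD 0.8 or 1.0 v 0.5, it rejects 6.0% or 8.6%. Mann-Whitney, which does not compare means there, rejects 17% or 36%.

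The main treatment comparison is not called into question.

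**What to change.** In the unpaired clause, replace the Mann-Whitney test as the response to unequal variance with Welch's t test. Since Welch also holds 5% when variances are equal, it can be used without a preliminary variance test. If a rank test is kept for unpaired comparisons, tie it to non-normality, as the following sentence does for the paired test. A possible wording is: *unadjusted between-group comparisons will use Welch's t test, or the Mann–Whitney U test when normality is not assumed.* This is one sentence, with no cost in data or participants.

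Optionally, and only if the biomarkers are expected to be right-skewed, state in advance that they enter the ANCOVA on the log scale at both time points. Under assumed lognormal data (25 per arm, log-scale effect 0.6 SD, log-scale correlation 0.6), power is about 73% on the log scale. On the raw scale it is 66%, 56%, 49% and 42% at log-SD 0.5, 0.8, 1.0 and 1.2. Effects would then be read as ratios instead of absolute differences.

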#### *Study aim*

To design an aquatic exercise program specific to knee osteoarthritis, with the goal of management of OA symptoms and the improvement of physical fitness. The PICO program is based around the first step for weight loss interventions in individuals with KOA being the control of pain and other symptoms. When KOA symptoms are controlled, patients learn that it is possible to live with the disease which in turn motivates lifestyle changes. The increase of physical activity due to lifestyle changes may then cause improvement in body composition. In this way 6 hypotheses are formulated: H1. 3 months of aquatic exercise will improve KOA symptoms (pain and stiffness) and physical function in obese individuals with KOA; H2. The gait parameters (gait speed, gait cycle, ground reaction forces and knee forces moments) of obese individuals with KOA can be improved by aquatic exercise; H3. Beyond fitness component and the exercises skills, aquatic exercise group classes can work as an educational component and to promote lifestyle changes. H4: The aquatic exercise program can improve mental status and quality of life. H5: The aquatic exercise program can cause a weight reduction or body composition change. H6: 3 months of aquatic exercise can have a positive effect on selected inflammatory biomarkers of KOA.

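### The Statistical analysis section lists several overlapping tests of the same treatment effect, all at two-sided 0.05 with none named as decisive, and it misdescribes the extra 6MWT model

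*Protocol article*

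**What the plan says.** The Statistical analysis section of the protocol article sets out these analyses of continuous outcomes:

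- **A.** Mean change "will be compared between groups using analysis of covariance adjusted for baseline values of the outcome".
- **B.** Unadjusted tests of the raw values: "Comparisons between groups (CG and AEG) at baseline and post intervention will be conducted by Independent-sample t-tests", or Mann–Whitney.
- **C.** Tests inside each arm: "Changes within group will be analyzed by paired" t-tests or the Wilcoxon signed rank test.
- **D.** For 6MWT only: "A mixed model analyses of covariance (ANCOVAs) will be conducted for interaction analyses adjusted for BMI with two within-participant factors of 6MWT (baseline" and post-intervention as the second factor, across the two groups.
- **E.** Multiple linear regressions "to understand the potential covariates that could improve the explanation of the variability of outcomes (6MWT, strength and KOOS dimensions".

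One threshold covers them all: "0.05 (2- tailed) for all analyses". No analysis is called primary or confirmatory, and no rule says which result stands if they disagree.

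The 6MWT is not peripheral. Under Outcomes, measures and instruments, aerobic capacity is part of the main outcome of physical function, and Table 2 shows that it is measured by 6MWT.

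Two other places bear on how the results may be read. Under Study aim, H1 reads "3 months of aquatic exercise will improve KOA symptoms (pain and stiffness) and physical function", with no mention of the control arm. Under Sample, the target is an improvement of about 25% from baseline to final measurement, not a difference between arms.

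**The concern.** For 6MWT, analyses A, B and D each give a between-arm p-value from the same two measurements, adjusted for the baseline value, for nothing, and for BMI respectively. For other continuous outcomes, A and B do so. When any of several correlated tests can serve as the result, the chance of a false positive exceeds the nominal 5%.

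The paired tests raise a different problem. They measure change in one arm, so they cannot separate the effect of the programme from natural course or from benefit that both arms share. A shared benefit is plausible, because the control arm attends a 12-session educational programme.

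The description of D is also wrong as written: baseline and post-intervention 6MWT are two levels of one within-participant factor, time. The sentence does not say when BMI is taken, although H5 expects weight or body composition to respond to treatment.

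Lastly, significance tests between arms at baseline examine a null hypothesis that randomisation makes true, and they inform no decision.

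**Working it through.** **The plan's own figure.** The dropout step reproduces: 20 / (1 − 0.20) = 25. The 20 itself cannot be reproduced, because no SD or pre-post correlation is given. Solving backwards at 80% power and two-sided 5% (t-based), 20 patients in a one-sample paired test imply a standardised change of 0.66, and 20 per arm in a two-arm comparison imply a standardised difference of 0.91. The text does not say which was meant; the effect it names is a baseline-to-final change.

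**Inputs.** From the document: alpha 0.05 two-sided for each test, and the forms of A to D. Assumed, because the document gives none of it: normal data with equal variances, pre-post correlation r, a BMI–baseline correlation of 0.2, and 20 or 25 analysed per arm (25 is half of the 50 in the Abstract; 20 is that number after 20% dropout). B was taken as the t-test.

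**Step 1: false positives among between-arm tests, no treatment effect.** A is the regression of change on arm and baseline; B is the t-test on the post value; D, correctly coded, is the regression of change on arm and BMI. Simulation with 40,000 trials per row:

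| Per arm | r | A alone | A or B (other outcomes) | A, B or D (6MWT) |
|---|---|---|---|---|
| 20 | 0.5 | 5.2% | 7.6% | 9.9% |
| 20 | 0.7 | 5.1% | 8.2% | 10.1% |
| 20 | 0.8 | 5.0% | 8.6% | 10.1% |
| 25 | 0.5 | 4.9% | 7.4% | 9.7% |
| 25 | 0.7 | 4.9% | 8.2% | 10.1% |
| 25 | 0.8 | 5.1% | 8.7% | 10.3% |

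Smaller runs (4,000 trials each, 20 per arm, r 0.3 to 0.7) gave 9.0% to 10.7% for the three 6MWT tests. Three independent tests would give 1 − 0.95³ = 14.3%; correlation keeps the rate below that. Each test alone stays near 5%.

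**Step 2: precision of D against A.** With equal variance σ² at both visits:

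- variance of a change score: 2σ²(1 − r)
- residual variance after baseline adjustment: σ²(1 − r²)
- ratio: 2(1 − r) / (1 − r²) = 2 / (1 + r)

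This is 1.33 at r = 0.5, 1.18 at r = 0.7 and 1.11 at r = 0.8. The ratio ignores any small contribution from BMI.

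**Step 3: what the paired tests depend on.** Suppose both arms improve equally, so the true difference between arms is zero (20 per arm, r 0.3 to 0.7):

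| Shared improvement (SD of outcome) | Exercise arm paired test significant | Exercise significant, control not |
|---|---|---|
| 0 | 2–3% | 2–3% |
| 0.3 | 19–38% | 15–23% |
| 0.5 | 42–79% | 18–24% |

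The first column is significance in the direction of improvement. The shared improvement is an assumption, and the document gives no value for it. The table shows how strongly the answer depends on it; it does not estimate an error rate for this trial.

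**The case against.** **A sound analysis is already in the plan.** The baseline-adjusted ANCOVA comes first among the inferential methods and covers continuous outcomes. Ranking of analyses is often left to a SAP, and this is a condensed article. That is right as far as it goes: silence about priority alone would be no finding. But this text positively prescribes the overlapping tests and sets them all at 0.05, so a SAP would have to override it rather than complete it.

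**Paired tests read as efficacy.** A reader might infer that within-arm changes will be presented as proof that the programme works. The document does not say so. It says only that such changes will be analysed, and it describes the study throughout as a randomised controlled trial, in which hypotheses are ordinarily read against control. The percentages in Step 3 are also not false-positive rates of the paired test, which there detects a real change; they mislead only if that change is credited to the exercise. What stands is that the reading is left open, and that a sample size set on within-patient change leans towards it.

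**A mis-specified mixed model.** A reader might infer that D is invalid. The sentence names the two measurements, the two groups and the interaction, so the intended group-by-time model can be recognised, and correctly coded it holds about 5%. Its lower precision is a matter of efficiency. BMI is an eligibility variable collected at screening, so a baseline covariate is the natural reading.

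**Scope.** The three-way overlap is confined to 6MWT. The regressions (E) are framed as explaining variability and were not counted. Baseline tests are poor practice but do not change the ANCOVA's error rate.

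**Conclusion.** The point holds in a limited form. The plan gives several routes to a claim about the same effect and does not say which counts. With no treatment effect, and with normal data, 20 to 25 per arm and r of 0.5 to 0.8 assumed, the chance that at least one between-arm test reaches 0.05 is about 9–11% for 6MWT and about 7–9% for other continuous outcomes, against 5% for the ANCOVA alone. These rates are per outcome. The exact figures rest on the assumptions; the direction does not.

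How often a paired test would mislead cannot be settled from the document, because it depends on an improvement shared by both arms that is not given. The 6MWT model is misdescribed, but correctly coded it is valid and merely less precise than the ANCOVA.

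**What to change.** In the Statistical analysis section:

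1. State that the baseline-adjusted ANCOVA, reported as a between-group difference with 95% CI, is the sole between-group inference for every continuous outcome.
2. Drop the unadjusted post-intervention tests and the baseline significance tests; describe the arms at baseline without p-values.
3. Report within-arm changes descriptively, without p-values.
4. Remove the 6MWT mixed model, or restate it as a sensitivity analysis with one two-level time factor and BMI fixed at baseline.

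Rewording H1–H6 as differences from the educational control would help but is optional.

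The cost is wording, and there are fewer analyses to run. The downside is that within-arm p-values are no longer available as results. With a single between-group test per outcome, the false-positive rate for that outcome returns to about 5%, whatever change the two arms share.

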## Discussion

The need to improve non-pharmacological intervention for patients with KOA is obvious, and aquatic exercise is an option for obese patients since it minimizes joint load. Although water exercise is frequently encouraged, relatively little research has been conducted in this area as compared to land-based exercise.

There are several strengths to the design of this study. The first one, is the detailed exercise prescription protocol concerning dosage (frequency, duration and intensity of the exercise), the fulfillment of overload and individuality principles of training (e.g., gradual increase of the number of sets and repetitions on strength training), and the control of exercise intensity during the sessions using rating perception effort scales (e.g., Borg RPE and Omni scales).

Secondly, the pool where the program will be delivered is easily accessed by train or bus. This aspect is crucial as the access to appropriate facilities and patient motivation to undertake water exercise, might be a barrier to adherence. Additionally, the fact of our sample being adult and not elderly should facilitate the displacement to our facilities.

Thirdly, the exercise program will be delivered by high qualified aquatic exercise instructors, all of whom shall be graduates in Sports Science at the Faculty of Human Kinetics who have specialized in exercise and health and fitness group skills. The exercise program will be delivered similarly to both classes regarding exercises, overloads and leading strategies according to the predefined plan. Four instructors will be organized in pairs, and each pair will take care of one aquatic exercise group during the entire program.

With the exception of the knee radiographs for OA diagnosis, all measures will be obtained in the same facility at the baseline and immediately after the end of the program. One barrier at each visit/measuring point will be the capacity to asses all participants in a short interval. Due to the specificity of the outcomes will be necessary to manage the schedule among four different labs. Therefore, to support the project, staff team includes one secretary responsible for administrative work, four technicians conducting the dynamometer tests, gait analysis, body composition and anthropometry assessments and one professional for collecting blood samples. Each technician received the responsibility to be specialized in two test’s group plus questionnaires and, to avoid inter-rater error, the same technician should lead its application in both assessments, baseline and post-exercise intervention. Participant adherence to exercise is one of the main challenges, therefore to avoid drop outs, motivational cues, intra-group social interaction, frequent telephone calls and the quality of instructors are the main strategies chosen to contribute to adherence rates. Besides, since our sample will include adults that may still be working which will create some difficulties in the definition of class schedules, one extra class, every 15 days, will be provided to enhance high compliance, and to allow that all participants might attend to 24 sessions during the 3 month period over which the study shall run.

One possible constraint to the success of the aquatic exercise programs would be the level of water skills of each participant. Although it is not necessary to know how to swim, the autonomy and the ability to apply power against the water are essential to get benefits from this type of activity, especially when performing strengthening exercises. Therefore some aquatic adaptation exercises will be introduced in the class format (Table 1).

Our study is based on the premise that individuals with KOA need a wide exercise intervention, adapted not only to the affected joint but to the health status of the patient, working the whole body and the mind simultaneously. In addition, we expect that aquatic exercise, beyond the improvement of KOA symptoms, can increase the symmetry between forces in the lower-limb joints (adduction/abduction and flexion/extension moments at knee and hip joints), so improving gait.

The format of the sessions, the study duration and the weekly frequency of exercise classes are organized in such a way as to make sure that this proposal is executable, not only for this project but also for future implementations by communities or in private pools. The sample size of this protocol are reduced because we consider that, before implementing the program in the general community, for public health, the exercise protocol should be validated by a very controlled process.

